### Outcomes

2.9

The primary outcome will be preference. Preference will be assessed by the following question: “After completing the training sessions, which one did you prefer?”. The preference will be assessed at T5. Secondary outcomes will be expectation, pain intensity, affect, and perceived effort, training volume, and cadence. Table 2 summarizes the assessment times and their respective outcomes.

**TABLE 2 pri70101-tbl-0002:** Outcome assessments.

Variables	T0	T1			T2			T3			T4
		A	B	C	A	B	C	A	B	C	
Primary outcome											
Preference											✓
Secondary outcome											
Expectation	✓										
Pain intensity	✓	✓	✓	✓	✓	✓	✓	✓	✓	✓	
Affect		✓	✓	✓	✓	✓	✓	✓	✓	✓	
Perceived effort			✓			✓			✓		
Training volume			✓			✓			✓		
Cadence			✓			✓			✓		

*Note:* A: Pre. B: Post: C: 24h. T0: Initial assessment. T1: Assessment will be performed respecting a 7‐day interval after the T0 assessment. T2 and T3: assessments will follow the same procedure as T1, with a 7‐day interval between each protocol (T1, T2 and T3), so that the patient will perform the other two training protocols (Figures 1, 2, 3). T4: assessment one week after the T3 assessment.

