### Pain Intensity

2.11

The intensity of widespread pain is assessed using the numerical pain rating scale, a self‐report instrument validated for Portuguese (Ferreira‐Valente et al. 2011). The Numeric Pain Scale has a sequence of numbers (from 0 to 10), where 0 represents “no pain” and 10 represents “the worst pain imaginable”. A reduction of 2 points in pain intensity is considered a minimal clinically important difference (Farrar et al. 2001). The numerical pain scale is answered by the patients at three time points: at the beginning, at the end, and 24 h after the end of each resistance training session.

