### Affect

2.12

The affective valence scale will monitor pleasure or displeasure during the three resistance training programs and will be conducted using the affective valence scale. The scale is quantified as follows: +5 to −5, corresponding, respectively, to the two antagonistic descriptors of the feeling during physical exercise and/or physical activity, which can be: “very good” and “very bad”. In addition, the affective valence scale presents other intermediate descriptors, which are: +3 = good, +1 = fairly good, 0 = neutral, −1 = fairly bad, and −3 = bad (Hardy and Rejeski 1989). The affective valence scale is completed by the patients at three times: at the beginning, at the end, and 24 h after the end of each resistance training session.

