### Statistical Methods

2.18

For the primary outcome (preference), the number of choices of the 3 types of training will be recorded as a percentage. For the analysis of the primary outcome, we will summarize the patient's preference in a contingency table, compare the proportions using the chi‐squared test, and finally verify the effect size of the observed differences. For the secondary outcomes, statistical analyses will be performed by a blind statistician using commercial software. The independent variables of group and time (T0, T1, T2, T3, T4) will be considered for each dependent variable: pain intensity, subjective effort, affect and satisfaction. The Kolmogorov–Smirnov test was used to verify the distribution of the data and the Levene test was used to analyze the homogeneity of variance.

A mixed design analysis of variance will be conducted for the primary and secondary outcomes with a normal distribution, with time as the within‐subject factor and group as the between‐subject factor. If the data are not normally distributed, the Friedman test is used. Time × group interactions and between‐ and within‐group differences were analyzed for all variables. Finally, the Bonferroni test is used in post hoc analyses to determine whether there are differences between‐groups at different intervention times. A 5% significance level and 95% confidence interval will be used for all statistical analyses.

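### For the secondary outcomes, the time factor is set as visits T0 to T4, which does not match the assessment schedule and leaves out the pre, post and 24 h readings of pain and affect

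*Protocol article*

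**What the plan says.** Section 2.18 (Statistical Methods) gives the levels of time explicitly: "The independent variables of group and time (T0, T1, T2, T3, T4) will be considered for each dependent variable". The dependent variables named there are "pain intensity, subjective effort, affect and satisfaction". The model is a mixed analysis of variance "with time as the within‐subject factor and group as the between‐subject factor", with a Friedman test as fallback. Bonferroni comparisons follow, "to determine whether there are differences between‐groups at different intervention times".

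The measurement sections describe a different repeated structure, which recurs in every session. For pain (section 2.11): "The numerical pain scale is answered by the patients at three time points: at the beginning, at the end, and 24 h after the end". For affect (section 2.12): "The affective valence scale is completed by the patients at three times: at the beginning, at the end, and 24 h after the end". Table 2 in section 2.9 carries the same three readings as sub-columns of T1, T2 and T3, coded "A: Pre. B: Post: C: 24h". Perceived effort (section 2.13) is rated once per session.

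Sections 2.5 and 2.6 say what the visits are. At T1, T2 and T3 the patient performs a protocol drawn at random from those not yet done, so that by T3 she has performed all three. T4 is a telephone call about preference.

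**The concern.** The factor in the analysis and the factor in the data are not the same. The visits include one (T4) at which none of the listed variables is recorded, a baseline (T0) at which only some are, and three crossover periods in which different patients perform different protocols. Differences between T1, T2 and T3 therefore show order, habituation or drift. They do not show what a session of one, two or three sets does to pain or affect.

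The readings that would show this are collected but have no stated place in the model, and nothing says which of the three readings stands for a visit. If that is settled after the data have been seen, the choice of reading, visit and factor is open. It matters for the article's aims too, since the Abstract and section 5 promise to relate preference to exertion and pain.

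**Working it through.** No calculated figure in the plan bears on this point. The check sets the stated factor levels against the schedule.

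**Step 1. Readings scheduled per visit**, for the four variables named in section 2.18 (Table 2, with sections 2.11 to 2.13):

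| Variable | T0 | T1 | T2 | T3 | T4 | Visits without data |
|---|---|---|---|---|---|---|
| Pain intensity | 1 | 3 | 3 | 3 | 0 | 1 |
| Affect | 0* | 3 | 3 | 3 | 0 | 2 |
| Perceived effort | 0 | 1 | 1 | 1 | 0 | 2 |
| Satisfaction | 0 | 0 | 0 | 0 | 0 | 5 |

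*Section 2.6 lists affect among the T0 assessments; Table 2 does not tick it.

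Cells: 4 variables × 5 visits = 20. Empty by Table 2: 1 + 2 + 2 + 5 = 10. If section 2.6 is right about affect at T0, 9.

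**Step 2. Readings the visit factor does not separate.** For pain and for affect: 3 sessions × 3 readings = 9 per patient per outcome. A factor with levels T0 to T4 has one level per session and cannot tell the three readings apart. Effort has 3 × 1 = 3 readings, so this step does not apply to it.

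**Step 3. What a T1 to T3 effect measures.** The protocol is drawn without replacement, so at each visit each protocol has probability 1/3. Assume, for illustration only, mean pre-to-post changes of 0, 1 and 2 points after 1, 2 and 3 sets. The expected change at every visit is then (0 + 1 + 2)/3 = 1.0. A simulation of 20,000 random orders gave 1.0006, 0.9978 and 1.0016 for the three visits. The visit effect is flat although the protocols differ by up to 2 points.

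**Step 4. What the interaction measures.** With group read as protocol and time as T1 to T3, time × group asks whether the difference between protocols varies with period. The question of interest is whether the change from before to after a session depends on the number of sets. That is protocol × within-session time, and section 2.18 does not name it.

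**Step 5. Outcome lists.** Section 2.9 declares expectation, pain, affect, effort, training volume and cadence as secondary. The list in section 2.18 omits expectation, training volume and cadence and adds satisfaction, which has no row in Table 2 and no measurement section.

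**The case against.** The best defence is that the visit list is shorthand. In Table 2 the pre, post and 24 h columns sit under T1, T2 and T3, the measurement sections fix those times, and section 2.18 promises within-group differences and comparisons at different intervention times. In a condensed article, the full plan may name the within-session factor. This stands so far as it limits the claim: the readings are not named as a factor, but the documents do not show that the response will go untested. It does not remove the point, because the levels of time are written out and do not fit the schedule.

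Other parts of the defence also hold:
- T0 is not empty throughout. Pain is measured there, and section 2.6 says affect is too.
- The within-session point covers pain and affect only. For effort, protocol with T1 to T3 is already close to what is needed.
- Section 2.18 also refers to secondary outcomes in general and to all variables, so expectation, training volume and cadence may be covered. The list is inconsistent with those sentences; it does not show that these outcomes are dropped.

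A reader might infer that no patient would have complete data over five visits, so that the analysis loses all 36. The documents do not support that: a visit at which nothing is scheduled is not missing data and would simply fall out of the model. A reader might also want to quantify a dilution from averaging the three readings, but no section says that they are averaged.

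**Conclusion.** The point holds for the secondary analyses. The stated time factor conflicts with Table 2: by that table half of the variable-by-visit cells (10 of 20) are empty, or 9 of 20 if affect is collected at T0. T1 to T3 represent period or order, and the within-session readings of pain and affect are not named as a factor. Satisfaction is listed for analysis without being measured.

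This is a stated rule that does not fit the schedule, not a detail left to a fuller plan. The cell count rests on Table 2 as printed; the flat visit effect in step 3 rests on the random draw and on assumed session effects, and shows direction only.

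A reader might take the point as a threat to the trial's main result. It is not: the chi-squared test on preference and the sample size of 36 do not use the time factor. Nor does it mean that protocols cannot be compared at all. A comparison of groups could still be made, but only after choosing a reading, and section 2.18 does not make that choice.

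**What to change.** Rewrite the secondary analysis in section 2.18 as follows:
- **Pain and affect:** specify protocol (1, 2 or 3 sets), period (T1, T2, T3) and within-session time (pre, post, 24 h), all within patient. Estimate the differences between protocols in change from pre-session to post and from pre-session to 24 h. Carry the same definitions into the non-normal fallback.
- **Effort:** protocol and period only, since there is one reading per session.
- **Visits:** remove T4 from the time factor. Use T0 only as baseline description, where the variable is measured there.
- **Affect at T0:** reconcile section 2.6 with Table 2.
- **Outcome list:** reconcile section 2.18 with section 2.9. Either delete satisfaction or, if it is a wrong name for another outcome, correct it; the documents do not say which. State how expectation, training volume and cadence are analysed.

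The cost is wording. The readings needed are already in the schedule, and no patient or visit is added. The change should be dated before the tabulated data go to the statistician.

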### Randomization, Allocation, Blinding, Patient Timeline, and Data Collection Methods

2.5

Randomization will be performed before each training protocol, taking into account the 3 different types of training protocols. The order in which the patient will perform the training protocol will be determined by a simple draw in an envelope containing 3 papers described as 1 series, 2 series, or 3 series. Therefore, if in the first session the patient draws the paper described as 1 series, in the following week this paper will be removed from the envelope and the same will draw 2 or 3 series, and so on.

In this way, all patients involved in the study will randomly perform the 3 types of protocols proposed in the study, and they will be their own controls. To avoid allocation bias, opaque sealed envelopes will be used, with sequential numbers on the outside of the envelope. This allocation will be made by Researcher B, who will not be involved in any other study procedures. Patients selected in the screening conducted by Researcher A who agree to participate in the research will be randomly assigned.

Regarding blinding, all assessments will be performed by Researcher A, who will not be involved in the interventions and will not participate in the delivery of the training protocol. Each patient will remain identified by numbers and not by name. In order not to compromise the blinding of the study, all patients will undergo the same assessment before and after the training session. Due to the nature of the proposed intervention (physical exercise), the therapist and patients will not be blinded to the intervention. Patients will be instructed not to disclose any information to other patients and/or researchers.

At the end of the T3 training protocol, with a 7‐day interval between these assessments, we will conduct T4, where each patient will be asked which training protocol they prefer. After T4, researcher D will tabulate the data, which will be delivered to researcher E, who will be responsible for the statistical analysis and who will not participate in the previous phases of the research (Figure 2).

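### Levene's test and a between-subject group factor are specified for a crossover, so the secondary F tests are not reliably at the stated 5%

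*Protocol article*

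**What the plan says.** All of the following is in the protocol article.

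- **Variance check.** Statistical Methods names one: "the Levene test was used to analyze the homogeneity of variance". A Kolmogorov–Smirnov test is named for distribution. Sphericity is not mentioned, and an epsilon correction is neither applied nor ruled out.
- **Model.** The secondary outcomes are to be analysed by a mixed-design ANOVA when they are normally distributed. The same sentence fixes the role of each factor: "with time as the within‐subject factor and group as the between‐subject factor". Bonferroni is used post hoc, and the Friedman test replaces the ANOVA only when data are not normal.
- **Factors.** "The independent variables of group and time (T0, T1, T2, T3, T4) will be considered" for pain intensity, subjective effort, affect and satisfaction.
- **Level.** "A 5% significance level and 95% confidence interval will be used for all statistical analyses".
- **Design.** The randomization section says that all patients "will randomly perform the 3 types of protocols proposed in the study, and they will be their own controls".
- **Readings.** Pain is scored "at the beginning, at the end, and 24 h after the end of each resistance training session"; the Affect section gives the same three times. Effort is recorded once per session.

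**The concern.** Levene's test compares spread between groups made up of different people. Here the 1-, 2- and 3-set readings come from the same women. The test is the natural companion of the between-subject group factor in the model, and both conflict with the crossover design.

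The F tests on repeated factors with three or more levels depend on sphericity, meaning equal variances of all pairwise differences. Equal variances of the readings do not ensure it. Pre- and post-session scores are taken close together and the third score 24 h later, so uneven correlations are plausible.

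At stake is the error rate of the secondary comparisons of training volume and time. A pass on Levene's test could be read as support for the ANOVA although it does not bear on the assumption that matters. The between-subject coding separately pushes some tests well below 5% and can push another well above it.

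**Working it through.** **Inputs from the article.** Significance level 5%, 36 patients, 3 protocols, 3 readings per session. The 36 agrees with the sample-size section: λ = 36 × 0.8² = 23.04, as printed. Correlations are not given, so all values below are assumptions.

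**1. Levene's test on paired data.** Simulated with 36 patients, three equal-variance readings and 20,000 runs, at nominal 5%:

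| Correlation between readings | Rejection rate |
|---|---|
| 0 (independent groups) | 5.3% |
| 0.5 | 2.6% |
| 0.7 | 0.6 to 0.7% |
| 0.8 | 0.2% |

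**2. Sphericity when all variances equal 1.** Let r1 be the pre/post correlation and r2 the correlation of either with the 24 h reading. The two orthonormal time contrasts have variances a = 1 − r1 and b = (3 + r1 − 4·r2)/3, and ε = (a + b)² / [2(a² + b²)]. For r1 = 0.9 and r2 = 0.2, a = 0.1, b = 1.033 and ε = 1.2844/2.1556 = 0.60. Variances are equal, yet sphericity fails badly.

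**3. Fully within-patient 3 × 3 interaction test (4 and 140 df), no true effects.** Simulated size; ranges are across repeated runs of 10,000 to 20,000, with between-protocol correlation 0 or 0.5 in the later runs:

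| r1, r2 | ε | Uncorrected | Greenhouse-Geisser |
|---|---|---|---|
| 0.5, 0.5 | 1.00 | 4.9 to 5.3% | 4.2 to 4.7% |
| 0.7, 0.5 | 0.91 | 4.9 to 5.5% | 3.7 to 4.4% |
| 0.8, 0.4 | 0.75 | 6.6 to 7.0% | 4.4 to 4.8% |
| 0.9, 0.2 | 0.60 | 8.2 to 8.6% | 4.6 to 4.9% |

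The theoretical ceiling, at the lower bound of ε, is P[F(1, 35) > F₀.₉₅(k−1, 35(k−1))]. This is 8.6% for a three-level factor and 12.8% for the four-df interaction.

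**4. The ANOVA as written.** A patient's protocol changes from session to session, so a between-subject group factor can be fitted only by entering each woman as three separate subjects: 36 × 3 = 108. I took time as the three within-session readings. Let ρ be the correlation of a patient's whole time profile between protocols.

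- *Group:* the expected numerator shrinks by (1 − ρ) and the error term does not, so size ≈ P[F(2, 105) > 3.083/(1 − ρ)].
- *Time:* the expected numerator grows by (1 + 2ρ), so size ≈ P[F(2, 210) > 3.039/(1 + 2ρ)].

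| ρ | Group, formula | Group, simulated | Time, formula | Time, simulated |
|---|---|---|---|---|
| 0.3 | 1.5% | 1.4% | 15.2% | 15.1% |
| 0.5 | 0.3% | 0.3% | 22.1% | 22.6% |
| 0.7 | 0.01% | 0.02% | 28.4% | 28.4% |

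The simulated columns are with sphericity holding within session, so the time inflation comes from counting patients three times. Across all covariances tried at these ρ, time ran at 15 to 29%, group at 0 to 1.7% and the interaction at 0 to 1.5%.

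If patients instead share only a constant level across sessions (30 to 70% of the variance), group runs at 0 to 1.2%, while time and interaction stay at 4.7 to 6.5%.

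**The case against.** **A missing sphericity correction is ordinary detail for a fuller plan.** This stands. A condensed article often leaves Mauchly's test or an epsilon correction to the SAP, and standard software supplies the correction. A reader might infer that the plan commits to an uncorrected ANOVA, but the text is silent. The point therefore rests on what the article does fix: an independent-groups variance check and a between-subject group factor, in a design where patients act as their own controls.

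**Inflation above 5% is conditional.** This also stands. A reader might infer that the planned F tests simply run too liberal. The documents give no covariance. Within-patient tests exceed 5% only if sphericity fails and no correction is applied, and mild departures cost almost nothing. In the ANOVA as written, the group test errs the other way, and so can the interaction.

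**Levene decides nothing.** Correct: only non-normality triggers the switch to Friedman. Deleting Levene alone would change no result. It is a symptom of the between-subject coding, which is the more consequential error.

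**Only secondary outcomes are affected.** Largely correct. The ANOVA sentence also mentions the primary outcome, but preference is a single categorical choice for which the same section names a chi-squared test.

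**Conclusion.** The point holds in a limited form. Levene's test is the wrong check for this crossover, and the between-subject group factor contradicts the design. Together they leave the secondary F tests without a reliable 5% level. The direction differs by test:

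- group is conservative, at 0 to 2% once a patient's sessions correlate;
- time can be strongly inflated, at 15 to 29% if whole time profiles correlate across protocols, but stays near 5% if only the patient's overall level is shared;
- a fully within-patient test without correction would run from about 5% to about 8 to 9%, depending on how far sphericity fails.

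These figures rest on 36 complete patients, normal data and assumed correlations, and on reading time as the three within-session measurements. They do not support a claim that all F tests exceed 5%. The chi-squared analysis of preference is unaffected.

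**What to change.** Delete the Levene step and replace the between-subject group factor. For pain and affect, fit protocol, time within session and their interaction, all within-patient; for outcomes read once per session, fit protocol as the within-patient factor. Either route works:

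1. **Linear mixed model** with within-patient covariance across all sessions and Kenward-Roger degrees of freedom. The structure must let a woman's readings in different sessions correlate. A fully unstructured 9 × 9 matrix has 9 × 10/2 = 45 parameters for 36 patients, so a product of a between-session and a within-session matrix is a practical fallback to name in advance.
2. **Fully within-patient repeated-measures ANOVA** with Greenhouse-Geisser correction on every F test with more than one numerator degree of freedom, applied whatever a pre-test shows.

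Greenhouse-Geisser on its own, with group left between-subject, would not be enough, because patients would still be counted three times.

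The cost is analysis wording only: no change to data collection, sample size or the primary analysis. The downside is slightly fewer effective degrees of freedom when sphericity holds; in the spherical case simulated, the corrected test ran at 4.2 to 4.7% instead of about 5%.

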### Load Test

2.8

To determine the training loads that will be used in this research, we chose to use a regression equation that predicts the value of the maximum load by performing a submaximal effort in the exercises proposed by the research, for the following reasons: minimizing the risk of injury, for better clinical applicability, and for the high degree of reliability compared to the one‐repetition maximum test in resistance exercises (O'Connor and Simmons 1989).

In addition, the study will evaluate women with fibromyalgia who have low exercise tolerance and high activity withdrawal (Vancampfort et al. 2024). To this end, we selected a submaximal effort test with the best reliability and reproducibility compared to the widely used one‐repetition maximum test, and thus found a prediction equation with the highest correlation and lowest standard error correlated with the one‐repetition maximum test, namely, one repetition maximum = load × [1 + (0.025 × lreps)] (Lacio et al. 2010).

The warm‐up program will be the same as that used in the conventional one‐repetition maximum test, where: each patient will perform a series of 5–10 repetitions, with a load equivalent to 40%–60% of the maximum load perceived before each proposed exercise. After respecting a 2‐min recovery interval after warming up, the subject will perform a series with the highest number of repetitions he/she can in each exercise. At this time, the evaluator will instruct the patient as follows: “Now, perform the highest number of repetitions you can”.

The evaluation of the loads in the exercises proposed in this research will be carried out in the T0 evaluation. The exercises, barbell bench press, front pulldown, 45° leg press, and seated leg curl, will be performed on supertech machines.

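### For pain, affect and effort, Section 2.18 names complete-block methods that lose any patient who stops before T3; a mixed model on all observed readings would keep her data

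*Protocol article*

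**What the plan says.** Section 2.18 (Statistical Methods) fixes the analysis of the secondary outcomes: "A mixed design analysis of variance will be conducted for the primary and secondary outcomes with a normal distribution, with time as the within‐subject factor". The training protocol enters in a different role, since the same sentence treats "group as the between‐subject factor". The fallback is also named: "If the data are not normally distributed, the Friedman test is used". The levels of time are the visits: "The independent variables of group and time (T0, T1, T2, T3, T4) will be considered for each dependent variable". The dependent variables listed include pain intensity, subjective effort and affect.

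Section 2.11 has pain read "at the beginning, at the end, and 24 h after the end of each resistance training session", and Section 2.12 gives affect the same three readings. With three sessions this makes nine readings per patient for each scale. Table 2 adds a T0 reading for pain, shows no pain or affect reading at T4, and has effort read once per session.

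Under Section 2.5 every patient performs all three volumes and serves as her own control. Section 2.8 describes the sample as "women with fibromyalgia who have low exercise tolerance and high activity withdrawal". The Introduction refers to high dropout and to patients' belief that exercise worsens symptoms. The Discussion links abandonment to earlier bad experiences with exercise.

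**The concern.** Classical ANOVA with a within-subject factor needs each patient's full vector. Friedman needs a full row of ranks per block. Neither can use a patient who has some cells and lacks others. Take a patient who draws 3 sets at T1, feels bad at 24 h and does not return. She has given complete readings for the 3-set session, yet a within-patient comparison of the three volumes by either method leaves her out.

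If patients stop because a session hurt, the missing patients are those whose readings show the least tolerance. The contrast between volumes is then too small, and a higher volume looks better tolerated than it was. The article intends to relate preference to exertion and pain (Section 5), so these readings matter beyond description.

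The issue is the choice of method, which Section 2.18 does state. The absence of a missing-data rule from a condensed article is not the point.

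**Working it through.** **The plan's own figure.** The article gives no number on this point. Its only calculation is the sample size for preference (Section 2.17). It reproduces: λ = 36 × 0.8² = 23.04; the 95% point of chi-squared on 25 degrees of freedom is 37.65; power is 0.804 at 36 patients and 0.789 at 35. It does not depend on ANOVA or Friedman.

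**Patients lost through withdrawal.** With overall withdrawal d before T3 (assumed), complete patients = 36 × (1 − d). For 10%, 20% and 30% this gives 32.4, 28.8 and 25.2.

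**Patients lost through single missed readings.** This applies only if all nine readings form one layout. With each reading missing independently with probability p (assumed), complete patients = 36 × (1 − p)⁹:

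| p | 9 readings | 10 readings (pain with T0) |
|---|---|---|
| 1% | 32.9 | 32.6 |
| 2% | 30.0 | 29.4 |
| 5% | 22.7 | 21.6 |
| 10% | 13.9 | 12.6 |

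**Bias, simulation 1.** All inputs are assumed: true 3-set minus 1-set difference in 24 h pain change 1.0 point; between-patient SD 1.0; residual SD 1.5; 36 patients in random order; a patient does not return after a rise above the threshold; 3000 runs.

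| Threshold | Complete patients | Complete-block estimate (SE) | All-data random-intercept estimate (SE) |
|---|---|---|---|
| 3 | 30.3 | 0.885 (0.365) | 0.998 (0.374) |
| 2.5 | 27.2 | 0.849 (0.367) | 0.993 (0.381) |
| 2 | 23.4 | 0.842 (0.400) | 1.017 (0.399) |

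The shortfall is 1 − 0.885 = 0.115 to 1 − 0.842 = 0.158, so about 12% to 16%.

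**Bias, simulation 2.** All inputs are again assumed: true difference 1.00; between-patient SD 1.2; residual SD 1.0; patient-by-volume slope SD 0 or 0.6; 600,000 patients per scenario.

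| Withdrawal | Complete | Complete-case | Mixed model |
|---|---|---|---|
| Random, 10% after each of the first two sessions | 81% | 1.00 | 1.00 |
| Depends on patient's general level only | 79% | 1.00 | 1.00 |
| Follows a bad response, weaker | 74% | 0.94 to 0.96 | 1.00 |
| Follows a bad response, stronger | 65% to 66% | 0.92 to 0.96 | 1.00 |

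Response-driven withdrawal gives 4% to 8% attenuation. Together the two simulations span about 4% to 16%. The other two mechanisms give none.

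**The case against.** **Group is called a between-subject factor.** If each patient-session were its own row, with pre, post and 24 h as time, a missed reading would cost one row. At 2% or 5% missing per reading, 108 × (1 − p)³ leaves 101.6 or 92.6 of 108 rows. The early leaver would keep her 3-set row, and simulation 2 gives 1.02 to 1.04 for a true 1.00, so no shrinkage. This shows that the loss depends on the layout. It does not rescue the plan. That layout treats three sessions of one woman as if they came from three women, against Section 2.5. It also does not match Section 2.18, where the levels of time are the visits. The between-subject label is a separate and more basic fault; once it is corrected, the methods named are still complete-block.

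**One missed reading discards everything.** A reader might infer this as a general rule. The article does not support it. Section 2.18 does not say which of the pre, post and 24 h readings enter, or that all nine enter together. Any loss is also confined to the outcome concerned.

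**Bias is certain.** A reader might infer this too. No withdrawal rate or SD is in the article, and the evidence on dropout concerns the population and exercise in general, not three single weekly sessions. Section 2.3 also excludes women who expect to be away during the four weeks. The bias is therefore conditional.

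**The effect is small.** This stands. The shift of 0.115 to 0.158 point is less than half its standard error and far below the 2-point important difference in Section 2.11. Root mean squared error from simulation 1 is about 0.38 against 0.37, 0.40 against 0.38, and 0.43 against 0.40.

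**A linear model on bounded scales is not ideal.** This is fair, and the fix includes a check for it.

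**Conclusion.** The point holds in a limited form. When the patient is the block, mixed-design ANOVA and Friedman exclude any patient who withdraws before T3 from the outcome concerned. Losing a patient through one missed reading holds only under a nine-reading layout. The volume contrast is attenuated by about 4% to 16% if withdrawal follows a bad session, and not at all if it is random or reflects only the patient's general level. These sizes rest wholly on assumed rates, thresholds and SDs. In the response-driven scenarios a mixed model recovered the true contrast, which is expected because withdrawal there depended on observed responses. The primary preference analysis and the 36 patients are untouched. Severity is minor to moderate, for secondary outcomes only.

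**What to change.** In Section 2.18:

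- Analyse pain, affect and effort with a linear mixed model fitted to all observed readings of every patient who performed at least one session.
- Use fixed effects for training protocol, reading within session (for pain and affect), their interaction, and period, with a random patient effect. Training protocol is then a within-patient factor.
- Check the residuals. If they are clearly non-normal on these bounded scales, add a rank-based or bootstrap check.
- Report the complete-block ANOVA or Friedman result as a sensitivity analysis, with the number of patients in each analysis.

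The cost is a change of wording and slightly more analysis work, with no new data, visits or patients. The model assumes that missingness depends only on observed data, which should be stated.
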